#### **2.2.2 Exclusion criteria**

- 1.) Intercurrent septic shock (fevers, broad spectrum anti-microbials, and needing vasopressors)
2. Active cardiac disease (such as STEMI/NSTEMI in last 2 weeks) or EF <35%
3. Prostate or breast cancer
4. Ongoing reason for catabolic state (active malignancy, HIV & opportunistic infection last 2 months)

5. Unable to engage in rehabilitation (due to significant neurological or orthopaedic issues)
6. Normal age-related level of serum testosterone in males (measured in early morning 6-9am)
7. Pregnancy or breast-feeding
8. Any known allergies to nandrolone components – including peanuts and soya and latex.
9. Elevated LFTs (ALT > 5x normal) and impaired bilirubin excretion
10. Polycythaemia (Hb > 165 males, > 150 females)
11. Nephrotic syndrome.
12. Athletes competing in international/national events.
13. Expected death within the next week

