### **Outcomes**

#### **Primary and secondary outcomes**

Primary outcome:

1. Time to walking with one person assisting (days from admission to ICU).
2. Hospital length of stay

Secondary outcomes:

1. Change in muscle strength as measured by the medical research council muscle strength (MRC) sum score - enrolment to discharge (note some ICU patients may not be able to participate in full MRC scoring, score will be extrapolated from available limbs) (9)
2. Grip strength (measured by hand held dynamometry)

3. Functional activity at hospital discharge (measured by physiotherapy staff using the Chelsea critical care physical assessment tool (CPAx (7)) and follow-up phone call at 3 months post discharge (using SF-36).
4. Hospital length of stay
5. Time to return to work (days) (for those working pre ICU).

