### **1.1 Statistical analysis and Sample size**

Trial will be prospectively registered on ANZCTR.

Efficacy of intervention will be analysed on an intention to treat basis. The analysis population is the intention to treat population defined as all study participants except for those who do not consent to use of data. There will be no imputation for missing data. A per protocol analysis will also be conducted including all participants with adherence to study medication of >80% of total study duration.

Normally and non-normally distributed data will be presented as mean and standard deviation (SD), and median and interquartile range (IQR), respectively. Between-group comparison of parametric data will be provided as mean difference and confidence interval and analysed using Student's t test. Between-group comparison of non-parametric data will be presented at median difference and analysed using the Mann-Whitney U test. For dichotomous data, frequencies and percentages will be presented and between-group analysis will use Fischer's Exact or Chi-squared test as appropriate. The numbers at risk in each group and the number and proportion of events observed will be reported, as well as the equivalent absolute risk difference, relative risk ratio and corresponding 95% confidence intervals. Survival time from randomisation until day 60, according to treatment group will be displayed as Kaplan-Meier curves and analysed using a log-rank test. Estimates of hazard ratios for survival, with corresponding 95% CI and P values, will be obtained from the Cox proportional hazards models incorporating treatment group alone, and independent covariates used in the multivariate models. Secondary analysis will also be conducted adjusting the primary outcome variable for prespecified baseline covariates (age, gender, APACHE-II score, BMI) in a transformed multivariable linear regression model including

baseline univariate variables with a  $p < 0.05$ . For all outcome analyses a two-sided P value of  $< 0.05$  will be considered significant.

Baseline variables recorded to demonstrate that the groups are comparable; if this is not demonstrated, *post-hoc* adjustments to correct for differences will be applied.

Sample size calculation: 60.

This is based on several different assumptions and outcome measures:

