1. Hospital length of stay, as sample of  $n=24$  per group has 80% power to detect a median difference of 3 days LOS (26 vs 23 days) with IQR 5.4 between independent groups (this is a conservative estimate as in the pilot, LOS results were 26 vs 36 days).
2. Time to walking with one-assist (ICU mobility scale). A sample of 24 per group has 80% power to detect a difference in proportions of 40 between the intervention and control groups, of patients walking with one assist at discharge (from a baseline of 27% in pilot).

To allow for loss to follow-up, the sample size number increased to 60.

Subgroup analysis: due to potential heterogeneity in patients, stratification based on MRC score,  $\geq 48$  (48 is an accepted cut off for ICU acquired weakness).

Economic evaluation:

An economic evaluation will be performed. Cost offsets from any reduction in LoS will be estimated separately for ICU stay and total hospital stay, and costed using hospital-specific per day costs. We will estimate QALYs using the SF-36 data converted to SF-6D using Australian population weights.(6)

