## **DATA COLLECTION, MANAGEMENT, AND ANALYSIS**

### **Data collection methods**

#### **Data Collection**

Data will be collected on a prespecified eCRF (RedCap - Research Electronic Data Capture - a secure web application for building and managing online surveys and databases) supported by a study-specific data dictionary and including checks of logical consistency and automatic query generation.

The following data will be collected:

- Age
- Gender
- ANZICS APD number

- Admission type (elective vs. emergency)
- ICU admission source (i.e. Emergency Department vs. ward vs. theatre vs. other hospital)
- Chronic APACHE co-morbidities
- APACHE-III admission diagnosis
- Illness severity based on the on the APACHE-II and III scores and risk of death, and “ANZ Risk of Death” models score
- ICU or HDA mortality
- ICU or HDA LOS
- Total duration of mechanical ventilation
- Total duration of vasoactive medication requirement
- Incidence and duration of renal replacement therapy
- Hospital mortality
- Post-ICU ward LOS
- Hospital disposition (home vs other acute care facility vs rehabilitation)
- ICU readmission
- Hospital readmission
- Day 60 mortality
- Inflammatory markers (CRP, Procalcitonin and WBC count at enrolment, ICU discharge and hospital discharge)
- BMI, weight at hospital admission, pre-admission medications.
- Baseline SF-36, FIM score and Barthel Index, to determine the patient’s pre-existing functional status (based on status two weeks prior to admission to ICU, from patient or surrogate).
- **Measurement of variables:**
  - **1. Laboratory tests**
    - Pregnancy test in women of child bearing age
    - Baseline: sex hormone binding globulin, testosterone.

- Routine blood tests will occur as planned by treating clinicians, and will collect:
- Haemoglobin, white cell count, albumin, urea and creatinine, alanine transferase.
- Lipids at baseline and at day 15-21.
- **2. Strength and weight measurements**
- a) Weekly: Hand grip strength, weight (kg) and MRC.
- **3. Other measures**
- Physiotherapy received - Duration of rehabilitation physiotherapy and mobility achieved (ventilation physiotherapy treatments will not be counted).
- Nutrition received - Caloric intake (kcal/total), Protein intake (g/total), Food intake (% of meals).
- **Follow-up**
- Phone call follow-up at 3 & 6 months using the SF-36 score , and asking about return to work (see script page).

*Pre-specified Subgroups:*

BMI at enrolment < 20

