Admission cause :sepsis, neurological, post surgical.

Data will be collected by trained research co-ordinators at each site. Patients and/or their next of kin will be asked to provide three possible points of contact (home and close family contact details) to the research staff prior to discharge. Day 90& 180 (post hospital discharge) SF-36 will be conducted over the phone by a trained assessor.

For data collected by research co-ordinators at each site, data quality and protocol standardisation will be optimised by arranging a start-up meeting, providing an early on-site monitoring visit, regular feedback to each centre via phone and the trial web-site, and a monthly newsletter. A complete study procedures manual will be produced. All study personnel will have 24 hour access to the study coordinating centre to resolve any questions.

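### Secondary outcome 1 is an unadjusted change in an MRC score that may be extrapolated from different limbs at enrolment and discharge, which adds a scoring artefact and gives up precision

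*Protocol*

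**What the plan says.** - Protocol, Primary and secondary outcomes: the first secondary outcome is "Change in muscle strength as measured by the medical research council muscle strength (MRC) sum score - enrolment to discharge". The attached note reads "note some ICU patients may not be able to participate in full MRC scoring, score will be extrapolated from available limbs". It does not ask for the same limbs at both ends of the change. Grip strength is the second secondary outcome, with no time point given.
- Protocol, Data Collection: "Weekly: Hand grip strength, weight (kg) and MRC". Both strength measures are therefore taken repeatedly.
- Protocol, 1.1 Statistical analysis and Sample size: "There will be no imputation for missing data". Continuous outcomes are compared by t test or Mann-Whitney. The planned covariate adjustment is for the primary outcome only and names age, gender, APACHE-II and BMI. Other adjustment is post hoc, if the groups turn out to differ at baseline.
- Same section, subgroup analysis: patients are divided by MRC score because "48 is an accepted cut off for ICU acquired weakness". No exception is made for extrapolated scores.
- Protocol, 2.2.2 Exclusion criteria, removes patients who are "Unable to engage in rehabilitation (due to significant neurological or orthopaedic issues"). One of the subgroups listed under Data Collection is "Admission cause :sepsis, neurological, post surgical", so neurological and surgical patients can still enter.

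**The concern.** An extrapolated sum score assumes that the untested limbs are as strong as the tested ones. Where that is untrue, the score is off by an amount that depends on which limbs were tested. A change score cancels this error only if the same limbs are tested at both ends, and the stated rule does not secure that. Part of a recorded gain or loss can then come from a different limb set. The same error can move a patient across 48 points.

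Two further points concern the same outcome. Filling an untested limb from a tested one is a form of single imputation, so the scoring note and the no-imputation sentence cannot both be followed literally. And the plan compares a raw change without using the enrolment score as a covariate, although that score is collected, which costs precision in a trial of 60 patients.

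At stake is a secondary outcome that bears directly on the stated hypothesis about muscle strength and on Aim 4.

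**Working it through.** **Nothing to reproduce.** The protocol gives no MRC effect size, SD, power or share of patients with untestable limbs. The sample size of 60 rests on length of stay and on walking with one assist. What follows is illustration under stated assumptions.

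**Assumptions not in the protocol.** Four limbs, three muscle groups per limb, each graded 0-5: 15 points per limb, 60 in total. Extrapolated score = 60 × (points in tested limbs) / (15 × number of limbs tested).

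**General result.** Let each arm score *a*, each leg *l*, and *d* = *a* − *l*. Strength does not change, and all limbs are tested at discharge, so the discharge score is 2*a* + 2*l*.

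- Both legs untestable at enrolment: enrolment score = 60 × 2*a*/30 = 4*a*. Recorded change = 2*a* + 2*l* − 4*a* = −2*d*.
- One leg untestable at enrolment: enrolment score = 60 × (2*a* + *l*)/45 = (8*a* + 4*l*)/3. Recorded change = 2*a* + 2*l* − (8*a* + 4*l*)/3 = −2*d*/3.

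| *d* (of 15) | one leg untestable | both legs untestable |
|---|---|---|
| 0 | 0 | 0 |
| 1 | −0.7 | −2 |
| 2 | −1.3 | −4 |
| 3 | −2.0 | −6 |

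If arms rather than legs are untestable at enrolment, the sign reverses.

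**Example.** Arms 13, legs 11, true total 26 + 22 = 48. Arms only: 60 × 26/30 = 52. Legs only: 60 × 22/30 = 44. With all limbs tested at discharge and no change in strength, the recorded change is 48 − 52 = −4 or 48 − 44 = +4.

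**Cut-off.** Arms 13, legs 10, true total 46. With one leg missing the score is 60 × (26 + 10)/45 = 48.0, so a patient truly below 48 is placed at 48 or above. In a simulation with assumed mean 44 to 48, between-patient SD 8, some random variation between limbs and *d* from 0 to 3, about 4% to 9% of patients with one leg missing fell on the wrong side of 48, and 7% to 32% of those with both legs missing. These are shares of affected patients, not of the trial.

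**Precision.** Assume equal SDs at both visits and enrolment-discharge correlation *r*.

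- Relative variance: change score 2(1 − *r*); unadjusted final value 1; ANCOVA 1 − *r*².
- ANCOVA against change score: (1 − *r*²)/(2(1 − *r*)) = (1 + *r*)/2, which is 0.75 at *r* = 0.5 and 0.85 at *r* = 0.7.
- ANCOVA against unadjusted final value: 1 − *r*², which is 0.75 at *r* = 0.5 and 0.51 at *r* = 0.7.

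The first ratio applies to MRC. The second applies to grip strength if a final value is compared. If grip is analysed as a change, the first applies there too.

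**The case against.** Several objections carry weight. The scoring formula and handling of partial scores are often left to a statistical analysis plan, and none is shown. That disposes of any complaint that details are absent; it does not dispose of what the stated rule permits. The scoring note is also a specific rule for an incomplete instrument, and the no-imputation sentence is a general one, so the conflict between them is mild and one clause settles it.

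The consequence is limited. Randomisation is stratified by site only, so the 48-point cut-off touches a subgroup analysis and not allocation. The limbs testable at enrolment are settled before treatment can act and are balanced between arms in expectation, and syringes are masked. Grip strength is a further strength outcome that needs no limb extrapolation.

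Stronger readings are tempting and not supported:

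- A reader might infer that limb sets will often differ because testing is harder at enrolment. The protocol expects some incomplete scoring but gives no frequency. It excludes patients who cannot engage in rehabilitation and expects most to have capacity to consent at enrolment.
- A reader might build a 12-point error. By −2*d* this needs *d* = 6 of 15 with both legs untestable: every leg muscle two grades below every arm muscle. The arithmetic is right, but the case is extreme. A leg may also be filled from the other leg.
- A reader might infer that the unadjusted change comparison is invalid. It is valid; the loss is one of precision.
- A reader might want the main analysis restricted to muscle groups scored at both visits. What can be tested at discharge arises after randomisation and may depend on treatment, and the restriction drops randomised patients against the intention-to-treat basis. It belongs in a sensitivity analysis.

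**Conclusion.** The point holds as a moderate weakness in a secondary outcome. The stated rule lets the recorded MRC change include an artefact of roughly 0.7 to 2 points with one leg untestable at enrolment only, and 2 to 6 points with both, for per-limb arm-leg gaps of 1 to 3 of 15 on an assumed 0-60 scale. It is zero when limbs are equally strong. Extrapolated scores can also put patients on the wrong side of 48. The number affected cannot be derived from the protocol.

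The error is mainly noise and misclassification. It becomes bias between arms only if treatment alters which limbs can be tested at discharge; the protocol does not show that it would, and the rule does not guard against it. The primary outcomes are not touched.

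Separately, the unadjusted comparison leaves precision unused. With equal SDs and *r* between 0.5 and 0.7, adjustment would have 75% to 85% of the variance of the MRC change score and 75% to 51% of that of an unadjusted final grip strength. Both the equal SDs and the correlations are assumptions.

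**What to change.** 1. Compare arms on the discharge MRC score with the enrolment score as covariate (ANCOVA), in place of an unadjusted t test or Mann-Whitney test on the change. Do the same for grip strength, using the enrolment measurement. This improves precision and handles chance imbalance in enrolment strength; it does not remove the extrapolation artefact, which is why step 2 is needed.
2. Record MRC by muscle group. Add two sensitivity analyses: one using only muscle groups scored at both enrolment and discharge, and one using only complete scores. Report the number of extrapolated scores by arm. Repeat the 48-point subgroup analysis using complete enrolment scores only.
3. Reword the no-imputation sentence so that it expressly excepts the MRC scoring rule.

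The cost is protocol or analysis-plan wording, a form that keeps muscle-group scores, and a little more analysis. The sensitivity analyses will contain fewer patients, and some patients will have no place in the repeated subgroup analysis. The main analysis need lose nobody on account of partial scoring.

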### **HYPOTHESES:**

Nandrolone will improve muscle strength and physical functioning at hospital discharge and at follow-up 3 months after enrolment.

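### Discharge CPAx is compared without adjustment and has no scheduled enrolment value, which gives up precision in a small, mixed population

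*Protocol*

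**What the plan says.** The hypothesis in the Protocol is that "Nandrolone will improve muscle strength and physical functioning at hospital discharge" and at three months. For function at discharge, secondary outcome 3 (Primary and secondary outcomes) is "Functional activity at hospital discharge (measured by physiotherapy staff using the Chelsea critical care physical assessment tool". CPAx is named nowhere else in the document.

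Strength is handled differently. Secondary outcome 1 is "Change in muscle strength as measured by the medical research council muscle strength (MRC) sum score - enrolment to discharge", so an MRC score at enrolment is required.

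The Data Collection list gives three kinds of information on starting condition:

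- SF-36, FIM and Barthel at baseline, which are "based on status two weeks prior to admission to ICU, from patient or surrogate".
- Serial in-hospital measures: "Weekly: Hand grip strength, weight (kg) and MRC".
- Under physiotherapy received: "Duration of rehabilitation physiotherapy and mobility achieved (ventilation physiotherapy treatments will not be counted").

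For analysis, section 1.1 (Statistical analysis and Sample size) states: "Between-group comparison of parametric data will be provided as mean difference and confidence interval and analysed using Student's t test", with Mann-Whitney for non-parametric data. Covariate adjustment (age, gender, APACHE-II, BMI) is planned for the primary outcome only. Adjustment after the fact is promised if the groups prove not to be comparable. Randomisation is stratified by site alone (Sequence generation).

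**The concern.** Patients qualify either by an ICU/HDU stay of at least five days or by weakness in the clinician's judgement (section 2.2.1). The protocol itself expects heterogeneity and plans a subgroup split at an MRC score of 48. Function at the start of treatment should therefore vary widely and should predict function at discharge. An unadjusted comparison leaves all of that variation in the error term.

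The function scales taken at baseline do not help much, because they refer to status before the illness that caused the weakness. What is at stake is the precision of one secondary outcome, which is nevertheless the scale attached to half of the stated hypothesis. An analysis plan could add a covariate later. It could not supply a bedside score that was never taken.

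**Working it through.** **Sample size used.** The protocol gives no power figure for CPAx. Its stated 24 per group can be reproduced from the walking outcome, reading the difference of 40 as percentage points (27% against 67%; two-sided 0.05; 80% power; no continuity correction):

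n = [1.960 × √(2 × 0.47 × 0.53) + 0.842 × √(0.27 × 0.73 + 0.67 × 0.33)]² / 0.40² = (1.383 + 0.544)² / 0.16 = 23.2, so 24.

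The total of 60 corresponds to 48 / 0.80, an implied loss of 20%. The range below is therefore 24 evaluable to 30 randomised per arm.

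**Gain against no adjustment.** Let r be the correlation between enrolment and discharge CPAx. The documents do not give it, so 0.3 to 0.7 is an assumption. Adjustment multiplies the variance of the treatment effect by 1 − r². The detectable difference in SD units (normal approximation) is

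d = (1.960 + 0.842) × √(2/n) × √(1 − r²).

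| r | Variance removed | d, 24 per arm | d, 30 per arm | Power for 0.5 SD, 24 per arm | Power for 0.5 SD, 30 per arm |
|---|---|---|---|---|---|
| no adjustment | – | 0.81 | 0.72 | 41% | 49% |
| 0.3 | 9% | 0.77 | 0.69 | 44% | 53% |
| 0.5 | 25% | 0.70 | 0.63 | 52% | 61% |
| 0.7 | 49% | 0.58 | 0.52 | 68% | 77% |

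The 0.5 SD effect is a reference point, not a protocol assumption. The approximation ignores the few degrees of freedom spent on the covariate and on site.

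**Gain beyond enrolment MRC.** Enrolment MRC is already required, so the case for a new CPAx score must be measured against adjustment for MRC. Let p be the correlation of enrolment MRC with discharge CPAx, and q that of enrolment MRC with enrolment CPAx. With both covariates,

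R² = (p² + r² − 2prq) / (1 − q²),

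and the standard error relative to adjustment for MRC alone is √[(1 − R²) / (1 − p²)]. The grid is assumed throughout: p 0.3 or 0.5, r 0.5 or 0.6, q 0.5 or 0.7.

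- Smallest gain (p = 0.5, r = 0.5, q = 0.7): R² = 0.294, ratio 0.97, a cut of 3%.
- Largest gain (p = 0.3, r = 0.6, q = 0.7): R² = 0.388, ratio 0.82, a cut of 18%.
- A middle case outside the grid (p = 0.4, r = 0.5, q = 0.6): R² = (0.16 + 0.25 − 0.24) / 0.64 = 0.266. The extra variance removed is (0.266 − 0.16) / 0.84 = 13%.

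**Gain from MRC alone.** This is p²: 9%, 16% or 25% of the variance for p = 0.3, 0.4 or 0.5, with no new data.

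**The case against.** The strongest reply is that nothing here is invalid. A discharge-only comparison of randomised groups is a legitimate secondary analysis, and its standard error already includes variation in starting function. That stands. Four stronger readings that a reader might infer also fail:

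- **That chance imbalance biases the result.** With 30 per arm the SD of the between-arm difference in starting score is √(2/30) = 0.26 SD, so a gap of at least 0.3 SD has a probability of about 25%. Such gaps are part of ordinary sampling error. They are the same precision loss seen from another side, not an additional harm.
- **That starting condition could never be corrected for.** Enrolment MRC, weekly grip and recorded mobility are partial substitutes, and the protocol allows later adjustment on recorded variables. Only the same-scale value is missing.
- **That CPAx is the sole measure of function at discharge.** The sample-size text also uses the proportion walking with one assist at discharge.
- **That an enrolment CPAx is ruled out.** The Data Collection list omits even the discharge CPAx, so it is not exhaustive, and a procedures manual is promised. What can be said is that the protocol schedules no enrolment score.

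It is also fair to object that r = 0.7 has no support in the document, and that r would be low if many patients score at the floor at enrolment.

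What the reply does not answer is that the substitutes are not planned as covariates for CPAx. MRC and grip also measure strength rather than function, and the protocol allows partial MRC scores to be extrapolated from the available limbs.

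**Conclusion.** The point holds as a loss of precision on one secondary outcome. The documents support three statements: CPAx has no scheduled enrolment value, the baseline function scales refer to a time before the illness, and the stated comparison uses no covariate. They do not support a claim of bias, of inflated type I error or of an irreparable comparison.

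The size rests on correlations that the documents do not give. Against no adjustment, the gain runs from slight (r = 0.3) to equivalent to nearly doubling the sample (r = 0.7: 1 / 0.51 = 1.96). Against adjustment for enrolment MRC, the extra benefit of an enrolment CPAx is more modest, and small if enrolment scores sit at the floor. The change is worth making because its first step costs nothing and its second very little.

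**What to change.** 1. In section 1.1, specify that discharge CPAx is compared by regression on arm, site (the stratification factor) and enrolment MRC. Mobility level may serve instead of MRC where a value was recorded before randomisation. The unadjusted test can remain as a supporting analysis. This needs no new data. Naming the covariate in advance is also preferable to an adjustment decided after baseline differences are seen.
2. Preferably, add one CPAx before the first injection to the Data Collection list and use it as the covariate. State who scores it: the protocol assigns physiotherapy staff to the discharge CPAx but does not say who performs the enrolment MRC. The cost is one short bedside score for each of 60 patients, the staff time for it, and an eCRF field.
3. If patients have already been enrolled without the score, keep enrolment MRC as the covariate for everyone, so that all patients are analysed in the same way.

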## 1. INTRODUCTION

### 1.1 Background and rationale

Intensive care patients can face significant health issues that extend beyond their Intensive Care Unit (ICU) stay. Despite recent advances it is estimated that one-quarter to one-half of long-stay intensive care survivors live with significant weakness as a consequence of their illness, resulting in impaired mobility and function.(1,2)

The loss of muscle mass in critical illness is related to immobility and a complicated process that causes muscle and nerve dysfunction called critical illness polymyoneuropathy. Another contributory factor is low levels of anabolic (muscle building) hormones such as testosterone – with testosterone levels in critically ill patients are extremely low, even in the recovery phase from acute illness. (3,4) One potential treatment may be to provide anabolic support in the recovery phase from prolonged critical illness.

This project aims to test whether giving a synthetic testosterone (nandrolone), will improve muscle strength in ICU survivors, when compared to placebo. Previous research has already established that early physiotherapy in the ICU can reduce length of stay and improve patients outcomes. In this study, both groups will receive standard care, which includes early physiotherapy. Nandrolone or placebo will be administered intramuscularly weekly for up to 3 weeks. Outcome measures will include hospital length of stay, time until the patient walks with assistance, muscle strength (globally and grip strength) as well as the patient's physical functioning at 3 months following enrolment.

The study design will be a double blinded randomised controlled trial, that will involve patients in WA Intensive Care Units (4 of the major units have already expressed interest in participating) and well as interstate if required.

The teams involved are multi-disciplinary, involving physiotherapy, dietitians, pharmacy as well as medical specialists. The investigators have already successfully conducted a pilot feasibility trial of a nandrolone versus placebo, showing that the intervention is safe and feasible.(5)

Given the large and increasing numbers of patients surviving intensive care both locally and internationally, (as illustrated recently with the post COVID syndrome) but with physical impairments, the results of this study would be of great interest to clinicians and patients alike.

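### The three-month follow-up is counted from enrolment in some sections and from discharge in others, and a discharge anchor lets time since randomisation differ between arms for secondary outcomes

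*Protocol*

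**What the plan says.** Two sections count the three-month functional outcome from enrolment. Section 1.1, Background and rationale, lists "physical functioning at 3 months following enrolment". The Hypotheses section states: "Nandrolone will improve muscle strength and physical functioning at hospital discharge and at follow-up 3 months after enrolment".

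Two other places count from discharge. Secondary outcome 3 (Primary and secondary outcomes) has a "follow-up phone call at 3 months post discharge (using SF-36", and Data Collection states "Day 90& 180 (post hospital discharge) SF-36 will be conducted over the phone by a trained assessor".

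The Blinding section (3 months) and the Follow-up item under Data Collection (3 and 6 months) give no starting point.

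For strength and function in hospital:

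- The MRC outcome is the change in "sum score - enrolment to discharge", without saying whether ICU or hospital discharge is meant.
- CPAx is read at hospital discharge.
- Grip strength has no time point in the outcome list.
- The measurement schedule reads "Weekly: Hand grip strength, weight (kg) and MRC".

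Aim 2 in section 1.2 is to shorten hospital stay, and length of stay is listed under the primary outcome. Aim 4 is to document changes in grip and limb strength during follow-up, counted from enrolment.

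**The concern.** There are two linked problems.

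First, the enrolment and discharge dates cannot both be the time of the three-month outcome. A site that follows the hypothesis would call earlier than a site that follows the outcome list, and the reported time point would be ambiguous.

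Second, discharge happens after randomisation and is something the treatment is meant to bring forward. If an outcome is timed from discharge and the stay is shortened, the arms are assessed at different times since randomisation. The comparison then mixes a treatment effect with a difference in recovery time. For readings taken at discharge itself, the arm with the shorter stay has had less time to recover, which may make a real strength benefit look smaller.

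**Working it through.** No stated figure is in dispute. The check is of dates, using the protocol's own lengths of stay.

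**Inputs**

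- Planned stay: 26 against 23 days (Statistical analysis and Sample size, item 1).
- Pilot stay: 26 against 36 days (same item). The text does not say which arm had which, but the size of the gap does not depend on that.
- Enrolment day *e*: not stated. Section 2.2.1 gives 5 ICU/HDU days as a minimum under one criterion, and the alternative weakness criterion has no minimum. I assume *e* = 5 to 14, counted from the same day as the stay.
- Randomisation is taken to fall on the day of enrolment, and MRC discharge to mean hospital discharge.

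**Step 1. Gap between the two anchors for one patient.** Gap = stay − *e*.

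| Stay (days) | *e* = 14 | *e* = 5 |
|---|---|---|
| 23 | 9 | 18 |
| 26 | 12 | 21 |
| 36 | 22 | 31 |

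**Step 2. Between-arm shift in the discharge-anchored call.** Shift = difference in stay. It does not depend on *e*.

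- Planning figure: 26 − 23 = 3 days. Calls fall about day 23 + 90 = 113 against 26 + 90 = 116 from admission. 3/90 = 3.3%.
- Pilot figures: 36 − 26 = 10 days. Calls fall about day 116 against 36 + 90 = 126. 10/90 = 11%.

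With calls fixed at days 90 and 180 from randomisation, the systematic shift is 0.

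**Step 3. Enrolment-to-discharge window for MRC.** Extra time in the longer-stay arm = shift / (shorter stay − *e*).

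- Planning figure: 3/(23 − 5) = 3/18 = 17%, to 3/(23 − 14) = 3/9 = 33%.
- Pilot figures: 10/(26 − 5) = 10/21 = 48%, to 10/(26 − 14) = 10/12 = 83%.

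These are shares of elapsed time under an assumed enrolment day. They show why the discharge readings are more exposed than the three-month call. They are not shares of strength gained: the protocol gives no recovery rate, so no bias in MRC points can be derived.

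**The case against.** The strongest reply is that the consequences are modest. On the planning figure the arms differ by 3 days in 90 at the three-month call, which is unlikely to matter much for the SF-36. Neither primary outcome is affected. Enrolment-anchored strength data are already an aim and are already collected weekly, and the choice of model could sit in the statistical analysis plan. All of that stands, and it limits the point to secondary outcomes. It does not resolve the contradiction, because the protocol itself states the call dates in two incompatible ways.

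A reader might infer more than the text supports:

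- *Patients leave at a similar, discharge-ready strength, so the effect is hidden.* The protocol does not say so. Its pilot baseline has only 27% walking with one assist at discharge, and it powers for a 40-point difference there, so it expects the arms to differ at that moment. Disposition includes rehabilitation and other acute facilities, so discharge need not mark a strength threshold.
- *A stated share of recovery is lost, such as 15–45%.* Any such figure needs an assumed enrolment day and treats elapsed time as strength gained.
- *In-hospital deaths make the discharge anchor worse.* A patient who dies in hospital has no day-90 SF-36 from randomisation either, so this does not separate the anchors.
- *QALYs cover unequal periods.* The economic evaluation paragraph states no horizon, so this would be an assumption.
- *Grip is read at discharge.* It has no stated time point at all.

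A fixed-time strength analysis has its own weakness. Weekly readings stop at discharge, so missing values depend on the same event that makes the discharge reading awkward.

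**Conclusion.** The point holds in a limited form. The contradiction over the follow-up anchor is explicit and needs no assumption. Its size for one patient is the remaining stay, 12 to 21 days at a 26-day stay, and this range rests on the assumed enrolment day. The between-arm shift of 3 to 10 days follows directly from the protocol's lengths of stay and is small against 90 days.

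For MRC change and CPAx at discharge the same mechanism is proportionately stronger. Understating a benefit is a possibility that depends on the stay actually being shortened and on strength still recovering at that stage. Its size is unknown. The change should be made because it is cheap and removes an avoidable ambiguity, not because a large bias has been shown.

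**What to change.** - Use one anchor, randomisation, with calls at days 90 and 180. Make section 1.1, the Hypotheses, secondary outcome 3, the Blinding section and both follow-up statements under Data Collection agree.
- For MRC and grip, add a baseline-adjusted repeated-measures analysis of the weekly values by time from randomisation. This serves aim 4 directly and gives grip a defined time point.
- Report discharge values of MRC and CPAx as supportive, and say whether MRC discharge means ICU or hospital. CPAx has no weekly schedule, so only its discharge value is available.
- Accompany the repeated-measures analysis with a sensitivity analysis for values missing after discharge.

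The cost is a wording amendment and a changed call schedule, with no new visits or measurements. The main downside is reliance on missing-at-random after discharge. A likelihood-based repeated-measures model uses the values observed and so fits the protocol's rule against imputation. If the sensitivity analysis imputes values, that rule needs a stated exception.
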